#### Secondary Outcome Analysis

For the main secondary outcome for the pregnancy phase of the trial, we will use a Chi-squared test to compare the proportion of women who have an adequate gestational weight gain in each group.

For the targeted analysis of urine biomarkers, the concentration of around 40 metabolites will be compared between baseline, 2 months in preconception and 24–26 weeks of pregnancy using repeated measures ANOVA or Friedman test with a Bonferroni adjustment for multiple comparisons. The correlation between the metabolite derived diet quality score and the C-HEI score will be evaluated using Pearson's correlation.

Although our sample size is fairly small, an exploratory multivariate analysis of non-targeted metabolome profiles will be realized using both unsupervised ‘natural clustering’ analysis and Supervised Random Forest classification.

For the other secondary outcomes, continuous variables will be assessed using Student's *t*-tests or Mann-Whitney tests as appropriate. Dichotomic variables will be analyzed using Chi-squared tests or Fisher's exact test as appropriate.

For participants who achieve a pregnancy prior to the 2-month food recall and/or 3-month preconception visit, lifestyle and anthropometric outcomes at the first pregnancy visit will be used to complete the preconception analysis. Women will be able to signal the occurrence of a pregnancy through the mobile application as soon as a period is missed. The application software will immediately notify the research team which will allow completion of data collection prior to the occurrence of significant pregnancy symptoms such as hyperemesis.

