### The Dearth of Evidence on Preconception Interventions

Several preconception lifestyle interventions have been developed using telephone coaching, face-to-face coaching, motivational interviews, and information technology and are being evaluated in ongoing clinical trials (31–33). Only one randomized controlled trial with published results has evaluated the effectiveness of a lifestyle intervention targeting non-infertile women with overweight or obesity in preconception, and none have included women's partners (34–36). In the preconception arm of the RADIEL trial (37), 228 women at high risk of GDM (with a personal history of GDM or a BMI ≥ 30) were randomized to standard care or a lifestyle intervention consisting of advice on diet and physical activity provided through personalized in-person meetings every 3 months. This study did not show a difference in the incidence of GDM between the control and intervention groups. However, these negative results could at least partially be explained by the higher pregnancy rates amongst women with obesity in the intervention group (52% of pregnant women were obese in the intervention group compared with 33% in the control group), which rendered the groups imbalanced when considering pregnancy outcomes (38).

Given the high burden of overweight and obesity on public health and the promising potential of lifestyle interventions targeting couples with overweight or obesity in preconception, further research is needed to elaborate and evaluate such interventions. The aim of this paper is to report the rationale and methods for the *Healthy for my Baby* trial, a randomized controlled trial evaluating the effectiveness of an intervention combining in person contacts with an information technology (IT) support to improve the lifestyle habits of women with overweight or obesity in preconception. This protocol is written in alignment with the 2013 SPIRIT statement (39). The SPIRIT checklist for this clinical trial is provided in Supplementary File 1.

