**For the Preconception Period:**

The primary objective of this trial is to evaluate the impact of the intervention on the diet quality of women measured with the Canadian Healthy Eating Index at 2, 4, and 6 months of follow-up.The secondary objectives of the preconception period are to evaluate the impact of the intervention on:- Urinary metabolomic indicators of women's dietary exposure at 2 months follow-up,- The diet quality of male partners at 2, 4, and 6 months follow-up,- The other lifestyle habits of women and their partners at 3 and 6 months (physical activity, sleep quality, anxious and depressive symptoms, and quality of life),- The anthropometric measures of women and their partners at 3 and 6 months (weight, waist circumference, and body fat percentage), and- The proportion of women and partners with a weight loss of at least 5% body weight at 3 and 6 months.

After completion of the primary outcome assessment, women and their partners who have achieved a pregnancy within 12 months following enrolment will be followed until the end of the pregnancy. Although, there is a potential for unbalanced study groups if the intervention has an impact on fertility, this exploratory follow-up phase will provide preliminary data on the impact of the intervention on lifestyle and clinical outcomes in pregnancy.

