The methodology of this trial presents several strengths. Firstly, our intervention was designed to be in line with both the UK Medical Research Council statement on the development and evaluation of complex interventions, and the Consort statement for the reporting of non-pharmacologic interventions (84, 85). Indeed, our intervention is based on a recognized behavior change model, specific intervention targets have been outlined, and the behavior change techniques at play have been well-described. These elements will improve the likelihood of intervention success and allow replication of the intervention if it is proven to be effective. Secondly, we have chosen to document the effectiveness of the intervention on metabolic risk factors in the preconception period prior to conducting a large clinical trial with sufficient power to detect differences in clinical outcomes. This first step in evaluating a complex behavioral intervention is in line with the Orbit recommendations (40) and will avoid a waste of resources if the intervention appears to be ineffective. This will also avoid the limitations in outcome assessment found in the RADIEL trial (38), where the measure of the primary outcome in pregnancy, when randomization took place in preconception, severely compromised the validity of the results. Thirdly, the choice of an explanatory randomized controlled trial design will provide good internal validity to document the effects of the intervention. Lastly, our methodology includes a detailed and systematic approach to recruitment, retention, and adverse event monitoring which will all contribute to the validity and success of the study.

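### Pregnancy-phase outcomes are compared without adjustment among women who conceived, although the article warns of imbalance in that subset and enrolment BMI is available

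*Protocol article*

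**What the plan says.** - **Population.** Under the preconception objectives, "women and their partners who have achieved a pregnancy within 12 months following enrolment will be followed until the end of the pregnancy". The pregnancy-phase outcomes are therefore seen only in women who conceive.
- **Tests.** Secondary Outcome Analysis: "we will use a Chi-squared test to compare the proportion of women who have an adequate gestational weight gain in each group". For the remaining secondary outcomes, continuous variables get a t-test or Mann-Whitney test, and "Dichotomic variables will be analyzed using Chi-squared tests or Fisher's exact test as appropriate". No covariate or stratum is named.
- **Warning and status.** The preconception objectives concede that "there is a potential for unbalanced study groups if the intervention has an impact on fertility", and the same sentence adds that "this exploratory follow-up phase will provide preliminary data on the impact of the intervention on lifestyle and clinical outcomes in pregnancy".
- **Precedent.** The Introduction reports of RADIEL that "52% of pregnant women were obese in the intervention group compared with 33% in the control group", and offers this as a partial explanation of that trial's negative result.
- **BMI as a risk factor.** The Introduction says that women with overweight or obesity are more prone to excessive gestational weight gain and to several complications, and that complication rates fall as pre-pregnancy BMI falls.
- **Design and data.** Randomisation is blocked but unstratified (Trial Design and Setting). Table 1 has height and weight at month 0, and randomisation is triggered only after the baseline assessment.
- **Safeguard.** The Statistical Analysis Plan section will report characteristics at the start of pregnancy to judge comparability. It also sets a 5% significance threshold for all analyses.

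**The concern.** Randomisation balances the women enrolled, not the women who later conceive. If the intervention changes who conceives, and does so differently for overweight and obese women, the two pregnant groups will differ in BMI mix even if the intervention has no effect on pregnancy outcomes. Because BMI predicts those outcomes, the difference in mix would then appear as an effect of the intervention, or would hide one.

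The article names this mechanism, but its only response is descriptive. Reporting characteristics at the start of pregnancy would show an imbalance and leave the estimates uncorrected. The covariate needed to remove the BMI part is measured before randomisation, so the intervention cannot have altered it.

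What is at stake is the point estimates. The Objectives section wants preliminary estimates of effects on maternal and neonatal outcomes, and the Discussion looks ahead to a larger trial on clinical outcomes of pregnancy. A bias from differential conception does not shrink as numbers grow.

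**Working it through.** **Planning figure.** The article gives no planning figure for the pregnancy phase. Its only one is for the primary outcome, and it reproduces. Reading the stated 10% as 10 points, with SD 13, two-sided 5% (sidedness is not stated) and 80% power:

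n = 2 × (1.96 + 0.84)² × 13² / 10² ≈ 26.5, so 27 per group. Then 27 / 0.80 = 33.75, so 34 per group and 68 in total.

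The present point does not touch this calculation.

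**Inputs for the bias**
- Obese share among pregnant women: 52% and 33% (RADIEL, as reported in the Introduction). Difference 0.19.
- Gap in outcome risk between obese and overweight women: not given in the article. Assumed 10 to 30 points, with 40 as an extreme.
- Pregnancies per arm: not given. Assumed 14 to 27.

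**Bias of the unadjusted difference with no true effect**

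bias = (0.52 − 0.33) × gap

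| Assumed gap (points) | Bias (points) |
|---|---|
| 10 | 1.9 |
| 20 | 3.8 |
| 30 | 5.7 |
| 40 | 7.6 |

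The sign depends on which arm has more obese women. With the RADIEL direction, and a lower rate of adequate gain in obese women, the bias runs against the intervention.

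**Bias against sampling error.** With 20 pregnancies per arm and rates near 50%:

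SE = √(0.5 × 0.5 × (1/20 + 1/20)) = 0.158, or 15.8 points.

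1.9 / 15.8 = 0.12 and 5.7 / 15.8 = 0.36, so the bias is 0.12 to 0.36 of a standard error.

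**Type I error.** Simulation with 200,000 replicates, no treatment effect, obese shares 52% and 33%, class rates centred on 50%, nominal 5%, 14 to 27 per arm:

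| Gap (points) | Unadjusted chi-squared |
|---|---|
| 10 | 4.2–4.4% |
| 20 | 4.5–5.0% |
| 30 | 5.1–6.0% |
| 40 | 5.8–7.5% |

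The ordinary Cochran-Mantel-Haenszel test stratified by BMI class stays at 4.8–5.0% throughout. At 114 per arm (an assumed size, half of RADIEL's 228) the unadjusted error would be 6.5–22% over the same gaps.

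**Power of the ordinary stratified test.** Simulation with 20 per arm, a true 30-point effect and a 10 to 30 point gap:

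| BMI mix | Stratified test | Chi-squared |
|---|---|---|
| Balanced arms | 46–50% | 45% |
| 19-point imbalance | 45–48% | 31–40% |

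The size of the stratified test in this set is 4.7–4.8%. These power figures depend on the underlying rate. If it is nearer 50%, the gap is only 10 points and the arms are balanced, the stratified test is slightly less powerful than chi-squared.

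**The case against.** Much of the case on the other side stands.

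- **Disclosure.** The article states the risk and calls the phase exploratory and preliminary in one sentence. This limits how much weight the point can carry. It does not justify ignoring an available covariate, since the same outcomes will be tested at 5%.
- **RADIEL.** A reader might infer that the trial repeats RADIEL's imbalance and so contradicts its own Discussion, which says the design "will also avoid the limitations in outcome assessment found in the RADIEL trial". The documents do not support that. The sentence continues: "where the measure of the primary outcome in pregnancy, when randomization took place in preconception, severely compromised the validity of the results". It concerns a primary outcome measured in pregnancy, and here the primary outcome is preconception diet quality, so the statement is accurate. Nor is any imbalance established. The article speaks only of a potential one, conditional on an effect on fertility.
- **Transfer of the 19 points.** RADIEL enrolled women with previous gestational diabetes or BMI of at least 30. This trial enrols women with BMI of at least 25. The 52% and 33% therefore illustrate a possible size and do not estimate what will happen here.
- **Denominators.** A reader might also infer that pregnancy and live birth rates will be computed on the wrong women. Nothing shows this, and the plan states intention-to-treat.
- **Cost in power.** An exact stratified test would be conservative. With 20 per arm, a 30-point effect and no imbalance, its size is about 3% and its power about 45–49%, against 54–55% for chi-squared. That tells against the exact version. It does not carry over to the ordinary test. The chi-squared figures here and in the power table above come from different assumed underlying rates, so they should be compared only within each set.
- **Partial remedy.** Adjusting for BMI leaves selection on age, parity, motivation or partner untouched. This is correct, and the plan should say so.
- **Unseen analysis plan.** A separate plan may add adjusted analyses. But the article is not silent here: it names the tests, and they are unadjusted.

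**Conclusion.** The point holds as a correctable weakness in a stated method. Outcomes observed only in women who conceive are compared by unadjusted tests, in a subset that the article says may be unbalanced, with a prognostic pre-randomisation covariate left unused.

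If conception differs by arm and BMI, the bias is 1.9 to 5.7 points for a 19-point obesity imbalance and a 10 to 30 point risk gap. Both the transfer of the imbalance and the gap are assumptions. At 14 to 27 pregnancies per arm the unadjusted type I error over those gaps is about 4.2–6.0%, so the nominal level is barely affected. The harm lies in the estimates handed on to a larger trial. The primary outcome and its sample size are unaffected.

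**What to change.** In Secondary Outcome Analysis:

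1. Compare adequate gestational weight gain between arms stratified by enrolment BMI class (25–29.9 and 30 or more), with the ordinary Cochran-Mantel-Haenszel test and a stratum-standardised risk difference with its confidence interval. Name the stratum weights in advance, so that a sparse stratum is handled by rule.
2. Analyse continuous pregnancy and neonatal outcomes in a linear model with arm and enrolment BMI. Use BMI at enrolment, not at conception, because the intervention is meant to change weight before pregnancy.
3. Keep the unadjusted tests as a supporting analysis.
4. State that the adjustment removes only the BMI part of selection into conception, and that the estimates remain exploratory and conditional on conception.

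The cost is wording. No new data, visits or participants are needed. The price in power is small at most, and where BMI mix does differ between arms the stratified test can gain power.

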**For Pregnancy:**

The main secondary objective of this phase is to explore the impact of the intervention on the proportion of women whose gestational weight gain conforms to the guidelines of the *National Academy of Medicine* recommendations (46).The other secondary objectives of the pregnancy period are to explore the impact of the intervention on:- The trajectory of dietary and lifestyle habits of women and their partners in the first, second, and third trimesters,- Women's urinary dietary exposure metabolomic profile at 24–26 weeks of pregnancy,- The change in the anthropometric measures (weight, body fat percentage, and waist circumference) of partners between the first and third trimesters,- The proportion of partners with overweight or obesity at study enrolment who have a weight loss of at least 5% body weight in the first, second, and third trimesters,- Perinatal morbidity indicators (gestational diabetes, hypertensive disorders of pregnancy, gestational age at delivery, delivery mode, birthweight, and neonatal hypoglycemia),- Fertility outcomes (viable pregnancy rate, spontaneous abortion rate, and live birth rate).

Women's diet quality will also be assessed based on metabolomic analysis of urinary samples. We will establish a profile of dietary exposure biomarkers, which will be used to compile a metabolite derived diet quality score (47, 48). This exploratory analysis will provide important data to support its use in a future larger multicenter trial.

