## Discussion

This innovative study will be the first to document the effectiveness of an intervention combining motivational interviews and IT support to improve the lifestyle habits of women with overweight or obesity without a history of infertility in the preconception period (34, 35). Furthermore, it will be the first study to include male or female partners in the evaluation of a preconception intervention (36). In addition to documenting the impact of the intervention on the lifestyle habits and anthropometric indices of partners, this analysis will provide insight on the impact of sex and gender in the response to interventions, and will allow us to explore whether the participation of both members of the couple is of added benefit for the achievement of lifestyle goals by each participant.

The body of evidence produced in this trial will be useful to guide future research endeavors on obesity prevention in preconception and pregnancy. This study will document the impact of the intervention on nutritional behaviors in preconception and will provide evidence regarding the plausibility of an effect of the intervention on health outcomes in the preconception period and pregnancy. If the intervention produces positive dietary changes which are sustained through the preconception period and pregnancy, a larger trial will be warranted to assess the effects of the intervention on clinical outcomes of pregnancy.

The use of urinary metabolomic profiling will also allow us to explore possible associations between epidemiological measures of diet and biological (metabolomic) indictors that may reflect dietary changes produced by the intervention. This profiling appears particularly promising as it is an objective means of evaluating dietary intake and is not subject to recall bias. If the metabolite derived diet quality score can be correlated with the C-HEI both in preconception and pregnancy, urinary dietary exposure biomarkers could be used as the sole measure of dietary intake and quality in future studies.

We will also document several measurements of the feasibility of targeting couples with no history of subfertility in the preconception period including recruitment rates, attrition rates, effective recruitment and retention strategies, and pregnancy rates within a 12-month preconception period. No similar study has been registered on the platforms clinicaltrials.gov or on the International Clinical Trials Registry Platform.

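### The test stated for urine metabolite concentrations compares time points and names no study group, so as written it does not estimate the intervention effect at 2 months

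*Protocol article*

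**What the plan says.** In the protocol article, under Objectives for the preconception period, the list of secondary objectives opens with "The secondary objectives of the preconception period are to evaluate the impact of the intervention on", and its first item is "Urinary metabolomic indicators of women's dietary exposure at 2 months follow-up". The pregnancy objectives list a separate item, "Women's urinary dietary exposure metabolomic profile at 24–26 weeks of pregnancy".

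The Secondary Outcome Analysis section gives the urine data their own method. It covers "the concentration of around 40 metabolites", and the comparison stated for these values is that they "will be compared between baseline, 2 months in preconception and 24–26 weeks of pregnancy using repeated measures ANOVA or Friedman test". A Bonferroni adjustment is added to that method. The metabolite-derived diet quality score is mentioned there only for its Pearson correlation with the C-HEI. The two-group tests come later and are introduced by "For the other secondary outcomes, continuous variables will be assessed using Student's".

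Urine is scheduled at baseline, at 2 months and at 24–26 weeks of pregnancy (Variables and Data Collection; Table 1). The Discussion values it because "it is an objective means of evaluating dietary intake and is not subject to recall bias".

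**The concern.** In a 1:1 randomised trial, the impact of an intervention on a marker at 2 months is a difference between arms. The method stated for the metabolite concentrations asks instead whether they differ between baseline, 2 months and mid-pregnancy. A change over those visits can come from season, from taking part in a trial or from pregnancy itself, and none of these is an intervention effect.

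The third visit adds a second problem. It exists only for women who conceive within 12 months and remain in follow-up. The Objectives section itself warns that arms may be unbalanced among women who conceive, if the intervention affects fertility. The 2-month objective does not need that sample.

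The primary outcome is self-reported diet in an open-label trial, and urine is the only measure of diet that is not self-reported. A randomised comparison of it is the natural support for the C-HEI result.

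**Working it through.** **1. Objective against method.** The table sets the article's own statements side by side.

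| Place | What is compared | Study group named? |
|---|---|---|
| Preconception objective, urine at 2 months | effect of the intervention | yes, by meaning |
| Primary Outcome Analysis, HEI | group, time and their interaction | yes |
| Secondary Outcome Analysis, gestational weight gain | proportions in the two groups | yes |
| Secondary Outcome Analysis, metabolite concentrations | three time points | no |

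The authors write the group out where they mean it. For metabolite concentrations they do not, and the t-test and Mann-Whitney rule covers the outcomes left after urine concentrations have received their own method.

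**2. The plan's own sample size.** No figure is stated for urine, so the trial size supplies the number of women. With a difference of 10 points, SD 13, two-sided alpha 0.05 (two-sided is assumed) and 80% power:

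n per group = 2 × (1.960 + 0.842)² × 13² / 10² = 26.5, rounded up to 27. Then 27 / 0.80 = 33.75, rounded up to 34 per group, or 68 in total. The stated figures reproduce. After 20% attrition about 54 women remain.

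**3. What the time test detects.** Simulation with 4,000 runs per scenario. Assumptions: 54 women, 27 per arm; 60% have a pregnancy sample, independently of arm; within-woman correlation 0.5; shifts in SD units. The time tests use complete triplets and no group term. The group contrast is a t-test on the change from baseline to 2 months in all 54. The share of runs rejecting is shown at alpha 0.05 and, in brackets, at 0.05/40 = 0.00125. The latter applies if the Bonferroni adjustment runs across 40 metabolites; the article does not state its scope.

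| Scenario | Friedman | RM-ANOVA, time | Group contrast |
|---|---|---|---|
| No effect of any kind | 4.6% (0.1%) | 4.8% (0.1%) | 5.0% (0.1%) |
| No intervention effect; both arms shift 0.5 SD | 70% (18%) | 83% (34%) | 5% (0.0%) |
| No intervention effect; pregnancy shifts both arms 1 SD | 99.7% (93%) | 100% (99.6%) | 5% (0.1%) |
| Arms differ by 0.8 SD, from shifts of +0.4 and −0.4 | 3.5% (0.1%) | 3.7% (0.0%) | 83% (31%) |
| Intervention arm alone shifts 0.77 SD | 40% (5%) | 54% (12%) | 79% (28%) |

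Rows two and three show the time test rejecting without any intervention effect. Row four shows it missing a real one because the arms cancel.

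**4. Women kept if complete blocks are required.** The documents give no conception rate. If 40% to 80% of the 54 reach a 24–26-week sample, 54 × 0.40 = 21.6 and 54 × 0.80 = 43.2, so about 22 to 43 women.

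A month-by-month version assumes that all women try from enrolment, that conception is at rate q per month, that 15% of pregnancies are lost before 24 weeks, and that 20% of women drop out. Complete triplets are then 68 × 0.80 × 0.85 × [(1−q)² − (1−q)¹²]. For q = 5%, 10% and 15% the bracket is 0.36, 0.53 and 0.58, giving about 17, 24 and 27 women.

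Baseline plus 2-month pairs, with the same 20% dropout and leaving out women who conceive before 2 months, are 68 × 0.80 × (1−q)² = 49, 44 and 39.

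**The case against.** **Shorthand.** Repeated measures ANOVA can carry a between-subject group factor, and the Primary Outcome Analysis uses a repeated measures ANOVA to compare HEI between groups. One sentence in a condensed article may simply omit the factor. That is possible, and the simulation does not settle it, because it assumes a time-only model. But the named alternative, Friedman, has no place for a group factor, and the sentence states what is compared. This is a method that is given and badly fixed, not a detail left to a separate plan.

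**The diet score.** A reader might infer that the urine objective cannot be answered at all. The documents do not support that. The metabolite-derived diet quality score has no between-arm test of its own and can fairly be read as one of the other secondary outcomes, which receive two-group tests. The point therefore holds for the metabolite concentrations.

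**Selection.** A reader might also infer that the plan restricts the analysis to women who conceive. No such rule is stated, and the article invokes intent-to-treat principles. The restriction follows only if the named tests are run in complete-block form; a mixed model or a pairwise baseline to 2-month contrast would avoid it.

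**Early conceptions.** Nor is it established that women who conceive before 2 months are dropped. The article substitutes lifestyle outcomes from the first pregnancy visit, and Table 1 lists urine under lifestyle habits. Table 1 schedules no urine at 6–8 weeks, so whether the substitution covers urine is unclear.

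**Reporting.** Nothing in the article says that a time contrast would be presented as an intervention effect.

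**Importance.** Urine is a secondary outcome, and the article describes the metabolite-score work as exploratory. This stands and limits the severity.

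**Conclusion.** The concern holds for the roughly 40 metabolite concentrations. As written, their test compares time points and does not estimate the between-arm effect that the 2-month objective asks for. This rests on the text alone.

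The loss of women who do not conceive is conditional on complete-block handling. Its size depends on unstated rates: about 17 to 43 women with all three samples across the assumptions shown, against about 39 to 54 for a baseline to 2-month comparison. The rejection rates illustrate direction and depend on the assumed correlation, shifts and 60% share.

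This should be fixed, but it does not threaten the trial. The primary analysis and the sample size are untouched, and the samples needed are already planned in both arms.

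**What to change.** - For each metabolite, compare concentrations between arms at 2 months, adjusted for baseline: ANCOVA, or a mixed model with a group-by-visit term. Use every woman with baseline and 2-month samples.
- Keep the Bonferroni adjustment and say what it spans. If it spans 40 metabolites, power per metabolite is modest (31% for a 0.8 SD difference in the simulation), which makes the next item more useful.
- State the same between-arm comparison explicitly for the metabolite diet score, so that it can be read beside the C-HEI result.
- Report 24–26 weeks separately, as an exploratory between-arm contrast among pregnant women.
- Say whether the first-pregnancy-visit substitution applies to urine.

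The cost is a few sentences of analysis text. No new data and no change in sample size are needed.
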